| Sample Size              | 42 participants                                                                                                                                                                                                                                                                                                                                                                                                                                                                                                                                                                                                                                                                                                                                                                                                                                                                                                                                                                     |
| Study Duration           | 1 January 2022 - 31 December 2024                                                                                                                                                                                                                                                                                                                                                                                                                                                                                                                                                                                                                                                                                                                                                                                                                                                                                                                                                   |

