Hand therapy offers a non-invasive and easily accessed first line intervention option for management of TF. Usual therapy management consists of a custom-made splint, hand activity modification with or without nonsteroidal anti-inflammatory medications (Ryzewicz & Wolf 2006). As a result of a Delphi European consensus published in a 'Guideline for Managing Trigger Finger' (Huisstede et al. 2014) three interventions and the order of use were suggested based on the evidence available in 2014. The consensus was that the initial intervention be splint wear, the second intervention a corticosteroid injection, and the third, proceed to surgery. In addition, the level of intervention chosen must take into consideration the severity, duration, and previous intervention history of the individual's TF.

The primary purpose of a splint to manage TF is to limit flexor tendon excursion through the A1 pulley (Evans et al. 1988). To limit tendon excursion, various hand-based and finger-based splints have been described. These splints usually immobilize one finger joint, either the MCPJ, proximal interphalangeal joint (PIPJ), or distal interphalangeal joint (DIPJ). The MCPJ blocking splint appears to be the most frequently used (Colbourn et al. 2008; Driksingen et al. 2017; Evans et al. 1988; Lindner-Tons & Ingell 1998; Patel & Bassini 1992; Tarbhai et al. 2012; Teo et al. 2018; Valdes et al. 2012). One publication immobilized the PIPJ (Teo et al. 2018) and two studies immobilized the DIPJ (Rodgers et al. 1998; Tarbhai et al. 2012). Tarbhai et al. (2012) compared a MCPJ blocking splint with a DIPJ blocking splint noted that the MCPJ blocking splint was preferred, with reasons cited as

being more stable, more comfortable, and less feeling of stiffness. Specifically, unlike DIPJ blocking splint that easily slipped off the finger, the MCPJ blocking splint allowed individuals with TF to perform tip-to-tip prehension which is important for hand function. The PIPJ blocking splint is the least studied splint for management of TF (Teo et al. 2018), which may be due to fabricate and fit issues.

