**b. Stages of Stenosing Tenosynovitis (SST)**

In this study, the Stages of Stenosing Tenosynovitis (SST) will be used to measure the participant's severity staging of TF. This is a grading system that divides TF into six stages with each stage is theorized to describe a different mechanical problem. Typically, Stage 1 is normal; Stage 2 is uneven finger movement; Stage 3 is triggering or clicking or catching; Stage 4 is locking of finger in flexion or extension, which can be unlocked by active finger movement; Stage 5 is locking of finger in flexion or extension, which requires application of passive force to unlock; and Stage 6 is locked finger in flexion or extension (Patel & Bassini 1992).

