### 3.6 Sample Size

A sampling of convenient method will be used to select eligible patients.

A prior TF research study (Teo et al. 2019) had reported that the result of pain score for pre-treatment = 4.65 (SD 2.39) and post-treatment = 3.40 (SD 2.44). G\*Power was used to compute statistical power analyses. Cohen-d effect size is 0.5175152.

Given Cohen-d effect size needs to be converted into Cohen-f effect size in order to determine the sample size of this study for two ways ANOVA, therefore, after converting digitally, the Cohen-f effect size is 0.259.

This proposed study will need 32 participants when a Cohen-f effect size of 0.26, confident level of 95%, significant level of 5%, and statistical power of 80% is applied.

Since a 10% dropout rate is anticipated, a total of 36 participants will be needed for this study. Of this total, 18 patients will be allocated to the RM group (RMG) and 18 patients to the MCPJ blocking group (MCPJBG).

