Once study eligibility is confirmed, the researcher will provide the information sheet and explain the study to the potential patient. If the patient agrees to participate, he/she will then be asked to sign the informed consent form and assigned an Identity Number (ID) for anonymity purposes. After signing the informed consent form, the Therapist A will proceed to administer the Demographic Questionnaire and other pre-intervention (baseline) assessments i.e., SST, DASH, COPM, VAS (pain, comfort, and satisfaction), and the Number of Triggering Events in Ten Active Fists. After completing the pre-intervention assessments, the participant will be asked to go to a designated counter near the therapy room for simple random assignment to the RMG or MCPJBG. Assignment will be done via concealed allocation with selection of an envelope by the counter staff. The envelope is prepared by the researcher. The envelope will contain either a paper printed with A which indicates RMG and B which indicates MCPJBG. After the participant returning to the therapy room, he/she will give the group assignment paper to the researcher. The researcher will fabricate either the RM splint or MCPJ blocking splint based on the randomization of group allocation. Each type of splint, the RM splint and MCPJ blocking will be fabricated using a low temperature thermoplastic material with 3.2 mm thickness, 1% perforation, and 100% memory.

For participants assigned to RMG, either a RME splint or a RMF splint will be fabricated. The splint design will be dependent on the participant's response to the RM pencil test carried out by the researcher. For this study, the RME pencil test will require the researcher to weave the pencil under the proximal phalanx of the affected finger(s) and over the dorsum of the adjacent fingers' proximal phalanx. For the RMF pencil test the researcher will weave the pencil over the dorsum of the proximal phalanx of the affected finger(s) and under the proximal phalanx of the adjacent fingers. With the pencil in place, the participant will be asked to open and close their fingers several times. The participant will be asked to choose which pencil test, RME or RMF lessened their pain and/or triggering. If the answer is the RME position, then a RME splint will be prescribed. Conversely, if the answer is the RMF position, then a RMF splint will be prescribed.

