### 3.9 Statistical Analysis Plan

Descriptive statistics will be used to summarize the Demographic data including age, gender, occupation, hand dominance, digit involved, associated medical conditions, and duration of triggering. Data will be analysed and described in total numbers, mean, and the pattern of data. Descriptive statistics will also be used to demonstrate the assessment outcomes including DASH, COPM, VAS (pain, comfort, and satisfaction), Number of Triggering in Ten Active Fists, and SST. An independent sample *t*-test, set at the significant level of 0.05 will be used to compare the baseline data between RMG and MCPJBG. A Two Way Mixed-ANOVA, set at the significant level of 0.05 will be used to compare the assessment outcomes, including DASH, COPM, VAS (pain, comfort, and satisfaction), Number of Triggering in Ten Active Fists, and SST between the RMG and MCPJBG. The interaction effect between these different variables will be analysed too. The results will show the percentage of variance in each effect regardless of size (Hypotheses 1 – 7).

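### Day-1 severity stage and symptom duration are recorded before allocation but left out of the between-splint model of a small, mixed, simply randomised trial (optional improvement)

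*Protocol*

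**What the plan says.** - **Background (1.1).** After listing splint, injection and surgery in that order, the protocol reports the consensus that "the level of intervention chosen must take into consideration the severity, duration, and previous intervention history" of the individual's condition. It also says that severe cases can lock, with sharp pain on unlocking.
- **Instruments (3.1.1).** On the six SST stages, "each stage is theorized to describe a different mechanical problem". A finger that locks persistently scores 10/10 on the triggering count, and with several affected fingers the worst one is scored.
- **Eligibility (3.3, 3.4).** Neither stage nor duration is restricted. Earlier treatment is restricted, through exclusions for recent steroid injection and A1 pulley release.
- **Allocation (3.8).** SST and the demographic form, which records duration, are completed first. The participant then goes to the counter for "simple random assignment to the RMG or MCPJBG". No strata, blocks or minimisation are stated.
- **Analysis (3.9).** A two-way mixed ANOVA "will be used to compare the assessment outcomes, including DASH, COPM, VAS (pain, comfort, and satisfaction"), triggering and SST. No covariate is named. Duration appears only among the descriptive summaries, and baseline data are compared by t-test.
- **Size.** Section 3.6 says "Since a 10% dropout rate is anticipated, a total of 36 participants will be needed for this study", 18 per arm. The synopsis says "42 participants". The two figures need reconciling; 36 is used below, with 42 as a check.

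**The concern.** The protocol's own text makes stage a plausible prognostic factor: locking is tied to pain in 1.1 and directly to the triggering score in 3.1.1. With about 18 patients per arm, the arms may differ by chance in how many fingers lock or are long-standing. Part of an apparent splint difference in pain, triggering or function could then be case mix.

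Variation between patients that stage and duration could explain also stays in the error term. An outcome's own baseline does not fully stand in for them: a pain or DASH score does not say whether the finger catches or locks, or for how long it has done so. The values are already in hand at allocation, so using them needs no new data.

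**Working it through.** **1. The plan's own sample size.** Section 3.6 gives "pain score for pre-treatment = 4.65 (SD 2.39) and post-treatment = 3.40 (SD 2.44"). Pooled SD = √((2.39² + 2.44²)/2) = 2.415, so d = 1.25/2.415 = 0.518 and f = d/2 = 0.259. Section 3.6 then applies "Cohen-f effect size of 0.26, confident level of 95%, significant level of 5%, and statistical power of 80" per cent. For a group-by-time test with two groups, m = 2 occasions and an assumed correlation ρ = 0.5 (the protocol states none):

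λ = f²·N·m/(1 − ρ) = 0.0676 × 32 × 2/0.5 = 8.65.

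On 1 and 30 df the power is 0.81, so N = 32 reproduces, and 32/0.9 = 35.6 rounds up to 36. At the same correlation the between-group main effect would need 90. The stated size therefore fits the group-by-time test.

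**2. What stage can do in that test.** Let S be stage (or duration). Suppose its effect on an outcome is b·S on Day 1 and (b + c)·S at Week 6. With two occasions the group-by-time test compares changes, and the change contains only c·S. The constant part b cancels. Both imbalance and residual variance therefore matter in that test only through c, the part that predicts change. In the group main effect, b stays.

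**3. Chance imbalance.** The documents give no stage distribution, so assume that 11 or 18 of 36 patients (about 30% or 50%) are Stage 4 or worse. For fixed arms of 18, the number h of such patients in one arm is hypergeometric and the gap is |2h − k|/18, with k = 11 or 18. For coin-toss allocation, sum over two independent binomials.

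| Allocation of 36 | Stage 4 or worse | P(gap ≥ 20 points) | P(gap ≥ 30 points) |
|---|---|---|---|
| Fixed 18/18 | 11 | 0.15 | 0.03 |
| Fixed 18/18 | 18 | 0.32 | 0.09 |
| Coin toss | 11 | 0.24 | 0.06 |
| Coin toss | 18 | 0.24 | 0.08 |

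With 42 patients in fixed arms of 21, P(gap ≥ 20 points) is 0.18 (13 of 42) or 0.22 (21 of 42). True simple randomisation of 36 yields exactly 18/18 in only 13% of allocations, and 12/24 or worse in 6.5%.

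**4. What such a gap does.** Four patients in 18 is 22 points. If locking fingers differed by an assumed 0.5 SD in change, the contrast would move by 0.222 × 0.5 = 0.11 SD. The standard error with 16 per arm is √(2/16) = 0.35 SD.

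**5. What adjustment gains.** Take N = 32 evaluable and two covariates of one df each, explaining a share R² of the variance of the analysed quantity (assumed):

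width ratio = √((1 − R²)·(N − 3)/(N − 5)) × t₂₈/t₃₀.

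Here (N − 3)/(N − 5) = 29/27 is the average penalty for chance correlation between covariates and arm, and t₂₈/t₃₀ = 2.0484/2.0423 = 1.003. Power uses λ × (27/29)/(1 − R²) on 1 and 28 df.

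| R² | Width ratio | Power (0.81 unadjusted) |
|---|---|---|
| 0.05 | 1.013 | 0.80 |
| 0.10 | 0.986 | 0.82 |
| 0.20 | 0.930 | 0.86 |
| 0.30 | 0.870 | 0.91 |

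Using 27 df for the adjusted model instead gives ratios of 1.015, 0.988, 0.931 and 0.871. Omitting the 29/27 penalty gives powers of 0.83, 0.85, 0.89 and 0.92. Break-even is near R² = 0.07.

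**The case against.** A reader might infer that the design contradicts the consensus it cites. It does not. That statement concerns the level of intervention on the path from splint to injection to surgery. Every participant is on the splint step, and nothing there says severity or duration should decide between two splint designs. Earlier treatment, its third element, is handled by exclusion. The SST stages are only theorised to differ, and no figure links stage or duration to splint response.

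A reader might also infer that the omission widens every interval. It does not. In the group-by-time test a constant effect of stage cancels, so the gain depends on an association with change that the documents do not quantify. At R² = 0.05 adjustment loses slightly.

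Other points against acting:

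- **Simple randomisation is valid.** Chance imbalance is already reflected in the p-value and interval, and the illustrative shift of 0.11 SD is about a third of a standard error. This stands, and it keeps the point optional.
- **Stage is not wholly absent.** Day-1 SST is the first response in the SST analysis, each outcome's own Day-1 value is in its model, and baselines are tested. This stands for SST. For the other six outcomes, no action is attached to the baseline t-tests, and with 18 per arm a non-significant test does not show balance.
- **Covariates may be in a separate SAP.** Possible. But section 3.9 already names the model, and a covariate choice is most credible when fixed before data are seen.
- **Blocked envelopes carry a risk.** Under 3.8 the researcher screens, obtains consent, prepares the envelopes and receives each assignment, and neither the researcher nor the therapists are blinded. Small fixed blocks would make some allocations predictable, which simple randomisation avoids. This stands in full.

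**Conclusion.** The point holds as an optional improvement in precision and face validity. It is neither a contradiction nor a source of bias. A mixed group of about 36 patients is allocated by simple randomisation, and the stated model ignores two pre-allocation measurements that could plausibly matter for pain, triggering, DASH, COPM, comfort and satisfaction.

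At an assumed 30% to 50% Stage 4 or worse, the chance of a gap of 20 points or more is roughly 15% to 32%, depending on prevalence and on how the arms are formed. The effect of adjustment ranges from an interval about 1% to 1.5% wider (R² = 0.05) to 7% to 13% narrower (R² = 0.20 to 0.30). These R² values are assumptions. For the group-by-time test they must be read as R² for change, and the documents give no such figure.

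**What to change.** In 3.9, pre-specify Day-1 SST stage (worst finger, as the triggering count already does) and log symptom duration as covariates in the between-splint comparison of the six non-SST outcomes. Enter stage as a single term, and give both covariates an interaction with time so that they act on the group-by-time contrast. For the SST outcome add duration only, because Day-1 SST is already the baseline response. On the demographic form, give the duration field a stated unit; at present it is open.

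The cost is wording and two degrees of freedom (one for the SST outcome), with a slightly wider interval if the factors prove weak. No visit, measurement or participant is added.

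Stratifying the envelopes by Day-1 SST stage in 3.8 is a further option. It is worth doing only with concealed, randomly varying block sizes and, preferably, envelopes prepared by someone other than the researcher. Otherwise the added predictability may cost more than the balance gains.

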## 1.2 SIGNIFICANCE

Occupational therapy is a health profession that helps individuals to participate in their activities of everyday life (World Federation of Occupational Therapists 2012). Occupational therapists working in the field of hand and upper limb-related rehabilitation have placed a major concern on helping individuals with various conditions, including TF to optimize function and participation in all areas of their life. A review of literature regarding the role of splinting for TF revealed two areas lacking evidence: (1) attainments of hand function and occupational performance after splinting; and (2) patient's perception about splint wearability (specifically comfort and satisfaction).

Previous studies that used a splint to manage TF have been mostly focused on the resolution of symptoms as classified and measured by a variety of instruments. Typically, severity has been classified by the Stages of Stenosing Tenosynovitis (SST) proposed by Patel & Bassini (1992) and applied by Alsancak et al. (2015), Colborn et al. (2008), Evans et

al. (1998), Rodgers et al. (1998), and Valdes et al. (2012) as well as Green's (Wolfe et al. 2011) grade classification applied by Teo et al. (2018). The pain associated with TF has been measured by Visual Analog Scale (VAS) (Alsancak et al. 2015; Tarbhai et al. 2012; Valders et al. 2012) and Numerical Pain Rating Scale (NRPS) (Colborn et al. 2008; Drikoningen et al. 2017; Teo et al. 2018). Grip performance has been measured by a dynamometer (Colborn et al. 2008). Triggering has been measured by patient-report of frequency of triggering (Tarbhai et al. 2012) and the frequency of triggering during performance of ten active finger open and closes (Colborn et al. 2008). Studies that focused on hand function and occupational performance evaluation were limited with instruments used include only the Quick-Disabilities of the Arm, Shoulder and Hand Outcome Measure (QuickDASH) (Drikoningen et al. 2017; Teo et al. 2018) and the Canadian Occupational Performance Measure (COPM) (Tarbhai et al. 2012).

Limited use of hand function and occupational performance evaluation was reported by Lunsford et al. (2017) via their systematic review. They recommended using a validated self-reported outcome measure to evaluate functional capacity of individuals with TF in daily life. Overall, occupational therapists practice client-centred care that is not solely focused on patients' symptoms, but also their satisfaction with hand function and occupational performance. Brown and Chien (2010) noted that when patients are encouraged to express their problems and to participate in activities which are considered as more important and relevant to them, more important occupational issues can be identified.

Perceptions about splint wearability, especially comfort and satisfaction require attention as well. Out of 10 studies about splint for TF, only two studies had investigated the splint wearability (Drikoningen et al. 2017; Tarbhai et al. 2012). Tarbhai et al. (2012) compared 6 weeks of full time wear of MCPJ blocking splint to DIPJ blocking splint in two evenly matched cohorts. After six weeks of MCPJ blocking splint wear 10/13 digits were fully or partially improved compared to 7/15 digits managed with a DIPJ blocking splint. Initially before splint wear both TF groups reported no loss of hand function but after wearing their respective splints reported it was awkward to work. Additionally, after splint wear, patient-rated function for the MCPJ blocking splint was 'good' (n=7/13) and 'fair' (n=5/13), while 7/15 DIPJ blocking splint wearers rated equally as 'good' or 'fair'. More patients (n=10/13; 77%) rated the MCPJ blocking splint as comfortable than 9/15 (60%) patients in the DIPJ blocking splint group. Stiffness of the PIPJ was also a concern with those who wore the DIPJ blocking splint. The author's recommendation was to use the MCPJ blocking splint due to comfort and greater success rate. Although the MCPJ blocking splint showed better results than DIPJ blocking splint, the involved MCPJ was restricted thus, it makes holding objects difficult. Among the comments from participants about MCPJ blocking splint were: 1) awkward hand positions when working; 2) longer time was needed to do things; 3) edges of splint was digging. Drikoningen et al. (2017) had reported mean satisfaction of 5.8 points (SD + 3.3, 10 rating-scale) for six weeks night-wear MCPJ blocking splint. After six week of splint wear, 18 from 34 participants had received corticosteroid injection due to unsatisfied or noncompliance to the splint, or triggering was unable to resolve.

In contrast, the originators of the finger-based RME splint encouraged early use of the injured hand for light tasks such as eating, writing, self-care to prevent the secondary complications of adhesion formation and finger stiffness. Collocott et al. (2020) noted that extensor tendon repair individuals who were from RME group show better hand functions compare to controlled active motion group at four weeks for the Sollerman Hand Function

Test. Hirth et al.'s (2011) reported that manual workers such as carpenters and electricians were able to perform work tasks while wearing the RME splint. This is because the design of the RME splint allows enough finger flexion (minus between 15-25° of MCPJ flexion of the involved finger) for holding a cup, writing, eating, or driving. With less restricted movement, individuals with TF may be able to return to work immediately and do work without interference from the RME splint.

A RM scoping review (Hirth et al. 2016) suggested that RM splints were widely used for various purposes beyond the original intent which was to protect extensor tendon repairs. Specifically, RM splints have been used for sagittal band disruption, boutonniere deformity, digital nerve repair, PIPJ flexion stiffness and so on. The review highlighted those six RM experts, consisting of three consultants had initiated the RM concept nearly 40 years ago. Of them, three had more than ten years of clinical experience with RM splint. They were consulted regarding their use of both RME and RMF splints for other applications, one of which was management of TF. These experts suggested that use of a RM splint for patients with TF conditions effectively limited the amount of flexor tendon excursion at the A1 pulley, decreased PIPJ stiffness after surgical release of the A1 pulley for chronic TF, and lessened pain both after TF release and non-surgical management. From this review, further study aimed at the effectiveness of RM splints for non-surgical management of TF are needed to determine if RM splints have a role in the management of TF.

Given MCPJ blocking splint has wearability issues and RM splint has the potential to treat tendon-related condition, there is a need to evaluate the effectiveness of both splints in a more detailed and functional manner from various perspectives. By including symptoms (TF severity, pain, and number of triggering events), hand function, occupational performance, perception of splint wearability (comfort and satisfaction), we can develop a more comprehensive management of TF. Every single domain of the International Classification of Functioning, Disability and Health (ICF) model is included in this study (Figure 1.0), to form a big picture about the individual's health condition related to body function as well as to their function within society (World Health Organization [WHO] 2002). From this study, we highlight the importance of hand function and occupational performance as well as splint wearability. By doing this, we will be able to know the effectiveness of the splint and how it brings meaningful improvement to the individuals with TF.

TF causes difficulties in hand function and limitation of participation in work and activities of daily living. MCPJ blocking splint uses principle of immobilization by blocking MCPJ of the affected finger. Immobilization restricts the finger movement and reduces inflammation of the flexor tendon. In contrast, RM splint permits use of finger. Individual with TF can continue to work with minimal interruption of productivity due to the disability and the intervention. Splinting is a non-invasive and less costly intervention as compared to other treatment interventions such as steroid injection and surgery. Splinting does not give patient much financial pressure. It also reduces the economic burden of the country by minimizing the need to take medical leave and undergone further treatments. RM splint may also help to promote speedy recovery and reduce the impact on the quality of life due to patient's disability. Providing effective treatment can improve wellbeing of an individual and the community.

RM splint is a potential splint that we suggested to use for TF. There is no study about the effectiveness of RM splint for TF thus far. Since RM splint has a lot of benefits from the perspectives of its design and function, RM splint is potentially effective to improve TF and subsequently, become a better choice of splint for TF management. The change from an immobilization splint to a more functional splint is an evolution to the splint management for hand condition. Patient does not need to give up their hand function to avoid interference to the process of healing. For therapists, RM splint is easy to fabricate, cost effective, and time efficient. Data collected through this study have the potential to raise awareness of the importance of using function-focus approach rather than disability-focus approach as well as improve information provision for therapist and clinician in terms of management plan and intervention. Outcomes of this study will be beneficial to both therapist and patient because better management can be outlined to patient. Overall, it will give good impact to both the profession and patient.

